###### Component 3: Needs‑based support

2.4.4.1.3

Carers will be encouraged to contact their facilitator when their care recipients experience changes in health status, dementia symptoms, or transitions in care type or care setting. Facilitators will support carers to navigate, access, and utilise appropriate health and aged care services and community resources in a timely manner to address emerging needs and prevent care crises.

Facilitators will also engage carers in structured coaching activities and provide individual coaching sessions based on carers’ needs. Coaching may be delivered online or in person, according to the carer’s preference. Facilitators will continue to support carers until identified needs have been adequately addressed. Initial coaching sessions will typically last 45–60 min, with follow‑up sessions lasting approximately 5–10 min. Both carers and facilitators will be encouraged to document coaching activities using the coaching tools.

###### Component 4: Carer feedback on care services

2.4.4.1.4

Facilitators will encourage carers to provide feedback on their experiences with care services during monthly peer support group meetings or through individual meetings with facilitators. Carers’ feedback will be discussed within participating organisations’ quality improvement meetings to inform service refinement and the development of more culturally tailored dementia care services for people living with dementia and their carers. Facilitators will also communicate organisational responses and quality improvement actions back to carers, closing the feedback loop.

##### The usual care group

2.4.4.2

A site-specific researcher will direct carers in this group to Dementia Australia and iSupport program website for dementia care resources including the online iSupport manual in their preferred language using a flyer.

#### Outcome evaluation

2.4.5

The scheduled time points for assessing the outcomes are outlined in Table 1 and detailed in the following sections. All instruments used in the outcome measures have been validated in English versions and have been translated and validated in the seven languages. Carer participants can choose their preferred language version in data collection.

**Table 1 tbl0001:** Time schedule of enrolment, interventions and assessment for participants.

	STUDY PERIOD													
	Enrolment	Allocation	Post-allocation											Close-out
Time point	-t_0_	t0 (baseline)	t_1_ (1 m)	t_2_ (2 m)	t_3_ (3 m)	t_4_ (4 m)	t_5_ (5 m)	t_6_ (6 m)	t_7_ (7 m)	t_8_ (8 m)	t_9_ (9 m)	t_10_ (10 m)	t_11_ (11 m)	t_12_ (12 m)
ENROLMENT														
Eligibility screen	X													
Informed consent	X													
Allocation		X												
INTERVENTINOS														
Psychoeducation														
Care support group														
Individualised support														
Feedback on services														
ASSESSMENT														
Demographic information		X												
Intervention effectiveness														
*Caregiver Qol: SF-12*		X						X						X
*Qol for care recipients: Qol-AD-Proxy*		X						X						X
*Caregiver self-efficacy: 8-item RSCSE*		X						X						X
*Caregiver social support: COPE Index-QS*		X						X						X
*Dementia related symptoms: RMBPC*		X						X						X
*Quality of care experience: QCE*		X						X						X
Intervention cost-effectiveness														
*Health service use*	X	X												X
*Resource usage: RUD*		X	X	X	X	X	X	X	X	X	X	X	X	X
*The incremental costs and gains in QALYs for caregivers and care recipients*		X						X						X

Allocation after baseline data collection; QoL: Quality of Life; SF-12: 12-Item Short-Form Health Survey; QOL-AD-Proxy: Quality of Life in Alzheimer’s Disease-Proxy; 8-item RSCSE: 8-item Caregiving Self-efficacy scale; COPE: Index-QS Carers of Older People in Europe Index-Quality of Social Support; RMBPC: Revised Memory and Behaviour Problem Checklist; QCE: Quality of care experience; Health service use: linked administrative health data from Data Linkage Services in Australia; RUD: Resource Utilization in Dementia Lite Questionnaire which will measure unplanned hospital admissions, emergency department use and the use of permanent residential aged care for care recipients; QALYs: Quality adjusted life years.

##### Demographic information

2.4.5.1

Demographic information about caregivers and their care recipients will be collected at baseline only by a site-specific bilingual and bicultural researcher.

##### Intervention effectiveness

2.4.5.2

We will collect data using a questionnaire survey with carer participants at baseline, 6 months and 12 months post-initiation of the intervention to measure intervention effectiveness. Participants can choose an online or hardcopy survey in their preferred language.

###### Primary outcome measures

2.4.5.2.1

Carers’ quality of life will be assessed using the 12‑Item Short Form Health Survey (Ware et al., 1996). The survey comprises 12 items that measure two summary domains: mental health–related quality of life and physical health–related quality of life, with higher scores indicating better quality of life. Care recipients’ quality of life will be measured using the proxy‑reported Quality of Life in Alzheimer’s Disease scale (Logsdon et al., 2002). Scale consists of 13 items, with higher scores reflecting better perceived quality of life.

###### Secondary measures

2.4.5.2.2

Secondary outcomes will include: (1) carer self‑efficacy, assessed using the 8‑item Caregiving Self‑Efficacy Scale (Ritter et al., 2022), with higher scores indicating greater self‑efficacy; (2) perceived quality of support, measured using a 5‑item support scale (Moholt et al., 2018), where higher scores reflect better support; (3) memory and behavioural problems of care recipients, assessed using the 24‑item Revised Memory and Behaviour Problem Checklist (Teri et al., 1992), with lower scores indicating fewer problems and reduced associated carer distress; and (4) quality of the care experience, measured using a 6‑item care‑proxy rating scale (Jemere et al., 2025), with higher scores representing a more positive care experience. In addition, healthcare utilisation outcomes, including hospital admissions, emergency department presentations, and permanent residential aged care placement, will be measured.

##### Process evaluation

2.4.5.4

The Integrated Promoting Action on Research Implementation in Health Services (i‑PARIHS) framework (Harvey & Kitson, 2016) will be applied to the process evaluation. The framework aligns with the UK Medical Research Council guidance for process evaluation of complex interventions (Moore et al., 2015). It conceptualises implementation as the interaction between four core constructs: innovation, recipients, context, and facilitation. These constructs provide a comprehensive lens to examine the factors influencing the implementation, embedment, and sustainment of the culturally tailored iSupport model, as described in the following sections.

First, the innovation construct emphasises the perceived relative advantage of an intervention over usual care, including its usability, credibility, and the extent to which its outcomes are observable in practice. In the context of this study, the culturally tailored iSupport model has been co‑designed with stakeholders, demonstrated effectiveness for carers and their care recipients, and shown acceptability in a pilot study (Xiao et al., 2025b, 2026a). Thus, the innovation characteristics of the model warrant further examination. In particular, how the iSupport is perceived in terms of its added value, usability, and fit within routine community aged care services needs to be explored when implemented at scale across a broader and more diverse population.

Second, the recipients construct emphasises the importance of developing in‑depth understanding of the individuals and groups involved in implementation, including their cultural values, language use, motivation, knowledge, skills, and available resources relevant to the intervention. Recipients in this study include carers from culturally and linguistically diverse backgrounds, iSupport facilitators and staff. Exploring the experiences of these recipient groups in engaging with the iSupport model is therefore essential to inform the refinement of evidence‑based implementation strategies.

Third, the context construct highlights the influence of local, organisational, and broader health and aged care system contexts on implementation processes and outcomes. Accordingly, this study will explore contextual factors shaping the iSupport model implementation, including policies, procedures, resources, staffing, education and training, workflows, and other organisational conditions that may enable or constrain staff engagement and commitment to embedding the iSupport model within routine practice.

Fourth, facilitation is conceptualised as an active and enabling ingredient for successful implementation and the achievement of desired outcomes. This construct focuses on the purposeful mobilisation of facilitation roles, skills, and strategies to assess and respond to the innovation, recipient characteristics, and contextual factors throughout the implementation process. Consistent with this framework, we previously co‑developed and pilot‑tested clearly defined facilitator roles, responsibilities, and a structured training program for iSupport facilitators who were staff members nominated by participating aged care organisations to deliver the intervention within their local service contexts (Xiao et al, 2025b). In the current study, iSupport facilitators will receive training, and their facilitation processes and implementation outcomes will be systematically monitored.

The process evaluation plan is summarised in Table 2 and described below. A mixed‑methods design will be employed, incorporating a descriptive qualitative approach using individual interviews and/or focus groups. Participants will include carers in the intervention group, iSupport facilitators, site leaders, and staff to capture diverse perspectives on the implementation and acceptability of the iSupport model. In addition, facilitators’ monthly implementation reports will be collected to identify site‑specific implementation challenges and strategies. Survey data will also be collected from carers in the intervention group to assess their satisfaction with resources and support provided during the study.

**Table 2 tbl0002:** A process evaluation plan informed by the i-PARIHS framework.

Elements	Explanation	Data collection methods
**The innovation**	The advantages, benefits and usability of the culturally tailored iSupport model from stakeholders’ perspectives.	Interviews or focus groups will be conducted with CALD carers, site leaders, facilitators, and staff involved in the culturally tailored iSupport model at 6 and 12 months.
**The recipient**	Cultural values, language use, motivation, knowledge, skills and resources among CALD carers and staff.	Baseline cultural and demographic information will be collected for CALD carers and staff; resources used in the study by carers, staff and organisations will be explored.
**The context**	Organisation’s policies, procedures, resources and support and aged care policies and funding arrangements that affect the culturally tailored iSupport model.	Interviews or focus groups will be conducted with CALD carers, site leaders, facilitators and staff at 6 and 12 months.
**The facilitation**	The actions/strategies, processes and outcomes in embedding the CT-iSupport; training and support for facilitators and staff; facilitators’ capabilities in implementation.	Monthly facilitators’ reports; site leaders’ comments on facilitators’ reports; interviews with site leaders, facilitators, staff and carers at 6 and 12 months.

i-PARIHS= Integrated Promoting Action on Research Implementation in Health Services; CALD= culturally and linguistically diverse.

#### Data collection

2.4.6

##### Data collection from carers

2.4.6.1

Site-specific researchers will collect demographic information at the baseline. They will also support carers to complete a self-administered survey at baseline, 6 months and 12 months post-initiation of the intervention. In addition, up to 30 carers in the intervention group will be invited to an interview at 6 months and 12 months post-initiation of the intervention.

##### Data collection from staff

2.4.6.2

Up to 30 staff involved in the delivery of the iSupport model will be invited to a focus group or an interview at 6 months and 12 months post-initiation of the intervention.

##### Data collection from the participating organisations

2.4.6.3

Data will be collected to examine organisational responses to the intervention innovation and contextual factors influencing implementation through multiple sources. First, facilitators responsible for delivering the iSupport model will document their activities and perceived outcomes using a structured portfolio. These portfolios will be reviewed monthly by site leaders to support implementation monitoring. Second, de‑identified Risk Appraisal Measure forms completed by carers will be submitted to the research team for analysis. Third, de‑identified coaching records completed by both facilitators and carers will be submitted to the project team on a monthly basis throughout the 12‑month trial period to capture the intensity, content, and responsiveness of coaching support. In addition, three monthly carer peer support meeting transcripts will be randomly selected from each peer support group for qualitative analysis to explore carers’ experiences and engagement with the peer support component.

#### Data analysis

2.4.7

##### Intervention effectiveness

2.4.7.1

Data analysis will be led by a statistician who will be blinded to group allocation. All analyses will be conducted according to the intention‑to‑treat principle, with participants analysed in their assigned groups. Multivariable linear mixed‑effects models will be used to examine differences in primary and secondary outcomes between groups over time. Given the repeated measurements for each participant, mixed‑effects models will account for both fixed and random effects within the hierarchical data structure. Fixed effects will include group, time, and group‑by‑time interaction terms, while random effects will model individual‑level variability in intercepts to account for within‑participant correlation. Models will be adjusted for baseline values of the outcome variables. Maximum likelihood estimation will be used to assess between‑group differences and changes over time.

Univariate mixed‑effects models will be fitted initially, followed by multivariate models incorporating variables identified as clinically relevant or statistically significant in univariate analyses to control for potential confounding. Model building will involve sequential addition and removal of covariates, with changes in model fit evaluated using log‑likelihood statistics to determine the final multivariate model. All statistical tests will be two‑sided, with statistical significance set at p < 0.05. Analyses will be performed using Stata version 16.1 and R version 4.2.2.

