#### Primary hypotheses

2.2.1

Compared to carers allocated to the usual care group, 1) carers receiving the culturally tailored iSupport model will report (a) at least a 5-point higher mean score on the mental component of the 12-Item Short-Form Health Survey and (b) an improved mean score on the physical component of the survey; 2) their care recipients will report an improved mean score on the Quality of Life in Alzheimer’s Disease-Proxy at 12-month follow-up.

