#### Study setting, participants and sample size

2.4.2

This study will be undertaken in community aged care settings managed by seven ethno‑specific aged care organisations located in three states in Australia. The estimated minimal sample size for carers in the study is 100 with 50 carers in the intervention group and 50 in the usual care group. This sample size is based on a primary outcome of the mental component of the 12-Item Short-Form Health Survey and an assumption of a 0.57 effect size reported in a previous trial using a multicomponent intervention for carers of people with dementia (Berwig et al., 2017), with an 80% power to detect a difference between means of 4.93 with a pooled standard deviation of 8.63 in the study. However, considering a 50% attrition rate in a 12-month trial in our previous project, we will need to recruit 150 carers to the trial or 75 carers in the tailored iSupport group and the usual iSupport group respectively.

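### With a carer random intercept as the only stated within-carer structure, the true error rate of the 12-month primary tests depends on correlations the protocol never gives: about 5% if its implicit assumption holds, otherwise roughly 3.5% to 11%.

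*Protocol article*

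**What the plan says.** Section 2.4.7.1 (data analysis, intervention effectiveness) specifies linear mixed-effects models with group, time and group-by-time as fixed effects. The random part is described as individual-level "variability in intercepts to account for" correlation within a participant. Models are adjusted for the baseline value and fitted by maximum likelihood, and tests are two-sided "with statistical significance set at p < 0.05". The section mentions no random slope, visit-specific variance, residual covariance structure or robust standard error.

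Outcomes are measured at baseline, 6 and 12 months (section 2.4.5.2 and Table 1). The primary hypotheses in section 2.2.1 are set "at 12-month follow-up". Section 2.4.2 sizes the trial "with an 80% power to detect a difference between means of 4.93 with a pooled standard deviation of 8.63" and sets recruitment at 150 carers "considering a 50% attrition rate in a 12-month trial in our previous project". The pooled SD of 8.63 is the only variability figure given. No correlation between visits appears anywhere.

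**The concern.** A random intercept with independent residuals has two covariance parameters. It implies equal variance at all visits and equal correlation between all pairs of visits (compound symmetry). The contrast that decides each primary outcome lies at the last visit.

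If correlation with baseline fades over the year, baseline explains less at 12 months than at 6. The residual variance is then larger at 12 months even when the raw SDs are equal. The model pools the two visits and so understates the 12-month variance. If carers leave gradually, 6-month records outnumber 12-month records and the pooled value moves further towards 6 months. The confidence interval is then too narrow and false positives exceed 5%. If the 12-month variance is the smaller one, the same model is conservative.

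This is separate from whether the baseline record is used as both response and covariate, because it remains under either correct way of handling baseline. With heavy attrition expected, the assumed covariance also governs how 6-month data inform missing 12-month values.

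**Working it through.** **The plan's own figure.** For difference 4.93, SD 8.63, two-sided 0.05 and 80% power: n per arm = 2 × (1.960 + 0.842)² × (8.63/4.93)² = 48.1, so 49 by the normal formula. By the noncentral t, power is 79.9% at 49 and 80.7% at 50. The stated 50 per arm reproduces. The protocol states no error rate for the mixed model beyond the nominal 5%.

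**Inputs that must be assumed.** Correlations are written 0-6 / 6-12 / 0-12 months, and SDs are relative to baseline. None of these is in the protocol.

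**Large-sample error rate, complete data.** Let r be the model-based SE divided by the true SE of the 12-month contrast. The actual error rate is 2 × [1 − Φ(1.96 r)].

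*Baseline as covariate only.* With equal SDs the residual variances are v6 = 1 − ρ(0-6)² and v12 = 1 − ρ(0-12)². The model uses their mean, so r = √[(v6 + v12)/(2 v12)]. For 0.65/0.65/0.50: v6 = 1 − 0.4225 = 0.5775 and v12 = 1 − 0.25 = 0.75, so v12 is 30% larger. The mean is 0.664, r = √(0.664/0.75) = 0.941, and the error rate is 6.5%.

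*Baseline as a response with a common mean.* Let ρ̄ be the average of the three correlations. With equal SDs, r² = (1 − ρ̄²)/(1 − 2ρ̄ρ(0-12) + ρ̄²). For the same pattern ρ̄ = 0.60, so r² = 0.64/0.76, r = 0.918, and the error rate is 7.2%.

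| Assumed pattern | Baseline as covariate | Baseline as constrained response |
|---|---|---|
| Equal correlations and SDs | 5.0% | 5.0% |
| 0.6/0.6/0.5 | 5.9% | 6.3% |
| 0.7/0.7/0.6 | 6.3% | 6.9% |
| AR(1) 0.6 | 6.8% | 7.7% |
| AR(1) 0.7 | 7.3% | 8.5% |
| AR(1) 0.8 | 7.9% | 9.3% |
| 0.7/0.7/0.6, SD up 10% by 12 months | 6.9% | 8.1% |
| AR(1) 0.7, SD up 20% by 12 months | 8.3% | 10.7% |
| Equal 0.6, 12-month SD 10% smaller | 3.8% | 3.5% |
| 0.5/0.6/0.6 | 4.1% | 4.4% |

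**Check with dropout.** Simulation under no effect used 75 per arm, 30% lost by 6 months and 50% by 12 at random, maximum likelihood, and 2,000 replicates (about ±1 point). Results are given as covariate, then constrained response:
- equal correlations 0.6: 5.8%, 4.5%
- AR(1) 0.7: 8.2%, 9.2%
- AR(1) 0.7 with SD up 20%: 9.4%, 11.0%
- equal correlations with a 10% smaller 12-month SD: 4.0%, 3.6%

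**How much is covariance and how much is estimation.** This uses the pattern 0.65/0.65/0.50, 150 carers and baseline as covariate. Ranges are across separate runs of 1,000 to 4,000 replicates. Nine further covariates is an assumption, since the protocol fixes no number.
- Random intercept, ML, no further covariates: 6.3-7.6%.
- Random intercept, ML, nine covariates: 8.1-8.4%.
- Random intercept, REML, nine covariates: 6.6-7.3%.
- Unstructured, ML, nine covariates: 6.1-6.6%.
- Unstructured, REML: 5.1-5.6% with nine covariates; 4.7-5.6% across the scenarios run with Satterthwaite degrees of freedom.

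**The case against.** The strongest objection is that nothing in the protocol shows compound symmetry to be wrong for these outcomes. A reader might infer that the 12-month SE is too small and that the test runs at 7-9%. The document does not support that as a fact: it gives neither correlations nor SDs by visit, and the direction can reverse. This stands, and it is why the point is conditional and both sides of the range are shown.

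A second objection is that part of the excess is not due to the random intercept. This also stands. With nine covariates, moving from ML to REML alone removes a substantial part of it.

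A third objection is that the article names a random intercept but does not say that residuals are independent. Both named packages can add a residual structure, and a full analysis plan, not shown, might do so. This limits the point but does not remove it. The sentence says how within-participant correlation will be handled and names intercepts alone, so an analyst following it would fit compound symmetry.

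**Conclusion.** The point holds conditionally. As written, the model ties the error rate of all the 12-month primary contrasts to an unstated and untested assumption of equal variances and equal correlations. The nominal 5% test runs at:
- about 5% if that assumption holds;
- about 6-9% if correlation fades over time;
- up to about 11% if the SD also rises;
- about 3.5-4.5% if the 12-month SD is smaller, or if 12 months correlates better with baseline than 6 months does.

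These figures rest on assumed correlations and SDs and on dropout at random. They also assume baseline is handled correctly, as a covariate or as a constrained response. Fading correlation is a natural expectation over a year, but the protocol offers no evidence of it, so no single figure should be quoted as the trial's error rate. A reader might also infer that freeing the covariance alone restores 5%. The runs do not show that: unstructured covariance under ML with nine covariates still gave 6.1-6.6%.

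**What to change.** In section 2.4.7.1, replace the random intercept for the repeated measures with an unstructured covariance over visits. Fit by REML with a small-sample degrees-of-freedom correction (Satterthwaite or Kenward-Roger). Include visit-by-baseline and visit-by-group terms, and state that each primary effect is the group contrast at 12 months. If a facilitator or peer-group random effect is added for other reasons, keep it alongside.

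The cost is a sentence or two and no new data. With baseline as a covariate only, the covariance for 6 and 12 months has 3 parameters instead of 2, one more than now. With baseline as a constrained response, three visits need 6 instead of 2, four more. The 12-month interval may become slightly wider. The abstract lists the trial as not yet recruiting, so the change can be made before outcome data exist.

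### Maximum likelihood is named for the treatment comparison, so at this sample size standard errors run about 1–2% too small for the model as specified and about 3–6% with nine added covariates

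*Protocol article*

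**What the plan says.** All of the relevant text is in section 2.4.7.1 of the protocol article, apart from the sample size.

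- Model: "Multivariable linear mixed"-effects models with arm, visit and their interaction as fixed effects and a random intercept for each participant. "Models will be adjusted for baseline values of the outcome variables".
- Estimator: "Maximum likelihood estimation will be used to assess" differences between groups and changes over time. REML is not mentioned.
- Covariates: "Model building will involve sequential addition and removal of covariates", using log-"likelihood statistics to determine the final multivariate model". The number of covariates is not given.
- Test: two-sided, "with statistical significance set at p < 0.05". No reference distribution or degrees-of-freedom method is named.
- Size (section 2.4.2): a minimum of 100 carers, raised to 150 "considering a 50% attrition rate in a 12-month trial in our previous project".

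**The concern.** ML estimates the variance components as if the fixed effects were known. The resulting variances are too small by a factor of roughly (N − p)/N, where N is the number of participants and p the number of fixed-effect parameters. This is negligible with many hundreds of participants, but not obviously so with about 75 at the primary time point and a covariate list that may grow.

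The bias runs in one direction and affects every outcome fitted with this model: intervals are too narrow and p-values too small. ML is the right fit for one task in the same section, the log-likelihood comparison of models with different fixed effects. The article also gives it a second task, the treatment comparison itself, where REML is the better fit.

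**Working it through.** **1. Inputs and the plan's own figure.** From section 2.4.2: difference 4.93, SD 8.63, 80% power. With two-sided 5% from section 2.4.7.1, n per arm = 2 × (1.960 + 0.842)² × (8.63/4.93)² = 2 × 7.85 × 3.064 = 48.1, so 49. Allowing for the t distribution gives 50 per arm, and the stated 100 is reproduced. Carers with 12-month data: 150 × (1 − 0.50) = 75.

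**2. Assumptions.** Baseline enters as a covariate, so the modelled outcomes are the 6- and 12-month values. The between-participant parameters are then intercept, arm and baseline (p = 3), plus one per added covariate. Four and nine added covariates are illustrations. Nine would be six terms for seven sites, one for spouse status and two for dementia stage if three stages are used. These are the randomisation factors in section 2.4.3; the article does not list them as model terms.

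**3. Closed form for a purely between-participant effect.**
SE(ML)/SE(REML) = √((N − p)/N).
Size of the ML z test = 2 × P(t with N − p df > 1.96 × √((N − p)/N)).
Example, N = 75 and p = 7: √(68/75) = 0.952.

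| Contributing N | p = 3 (no added) | p = 7 (four added) | p = 12 (nine added) |
|---|---|---|---|
| 75 | 2.0% short, size 5.9% | 4.8%, 6.6% | 8.3%, 7.7% |
| 100 | 1.5%, 5.7% | 3.6%, 6.2% | 6.2%, 6.9% |
| 150 | 1.0%, 5.4% | 2.4%, 5.8% | 4.1%, 6.2% |

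**4. Why the 12-month contrast is affected less.** It also draws on within-participant variation, where few parameters are fitted. With everyone seen at both visits and correlation ρ between them, the squared ratio is ½[(1 + ρ)(N − p)/N + (1 − ρ)(N − 2)/N]. For N = 75 and ρ = 0.6:
- p = 3: ½[1.6 × 0.960 + 0.4 × 0.973] = 0.963, root 0.981.
- p = 9 (six added): ½[1.6 × 0.880 + 0.4 × 0.973] = 0.899, root 0.948.

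Simulation of the same two cases gave 0.981 and 0.947.

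**5. Simulation of the stated model with no treatment effect.** Setting: 75 carers at 12 months, between 76 and 150 at 6 months, correlation 0.6, Monte Carlo error of size about 0.45 points.

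| Added covariates | SE(ML)/SE(REML) | Size of ML z test |
|---|---|---|
| 0 | 0.98–0.99 | about 5–5.5% |
| 4 | 0.96–0.98 | 5.3–6.2% |
| 9 | 0.94–0.97 | 6.4–7.2% |

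Other runs show the scatter. With nine covariates and 3,000 data sets per setting, size was 7.5%, 6.2% and 5.0% with 75, 112 and 150 carers seen at 6 months (SE ratios 0.94, 0.96, 0.97). The worst corner, ten covariates with only 75 carers contributing, gave a shortfall of 6.6–7.7% and size of 7.3–7.6%.

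**6. After the change.** REML with t degrees of freedom gave 4.4–5.5% across all scenarios run with 4,000 data sets each (Monte Carlo error about 0.35 points).

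**The case against.** **The headline risk is easily overstated.** A reader might infer that standard errors are flatly 4–6% too small and that every test runs above 6%. The article does not support that. For the fixed effects it actually names, the shortfall is 1–2% and the size about 5–5.5%. Larger figures need covariates whose number it does not state. This objection stands, and the figures must be given as ranges.

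**The sample is not simply 75.** The intention-to-treat mixed model keeps carers with a 6-month value only, so between 75 and 150 contribute. This also stands, and the simulated ranges allow for it.

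**Small-sample degrees of freedom are not excluded.** The article is silent on the reference distribution, and that detail may sit in an analysis plan not shown. Its absence is therefore no finding, and the size figures hold only for a z reference. However, a t reference alone does not repair the ML variance: in the closed form with N = 75 and p = 6 to 8, size is still 6.0–6.4%. The choice of ML is stated, and Kenward-Roger is built on REML, so an analysis plan using it for the treatment effect would depart from this text.

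**ML has a legitimate reason to be there.** Comparing different fixed effects by log-likelihood calls for ML. That justifies it for model comparison, not for the reported effect.

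**Clustering might seem to aggravate the problem.** A reader might add that a facilitator or peer-group variance would rest on few groups. The stated model has participant intercepts only, so this does not apply to the plan as written.

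**Conclusion.** The concern holds as a modest one. The article assigns ML to the treatment comparison. With about 75 carers at 12 months this understates the standard error by about 1–2% for the specified model, 2–4% with about four added covariates and 3–6% with about nine, and slightly more if no carer contributes a 6-month value alone. With a z reference, the 5% test runs at roughly 5–7%.

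These figures assume 50% attrition, baseline as a covariate, and covariate counts fixed in advance. They do not include any effect of data-driven covariate selection, which is a separate matter that changing the estimator would not cure.

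**What to change.** Replace the estimation sentence in section 2.4.7.1 with wording such as: *Treatment effects, standard errors, confidence intervals and tests will be taken from the final model refitted by REML with Kenward-Roger (or Satterthwaite) degrees of freedom; ML will be used only to compare models with different fixed effects by log-likelihood.*

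Both named packages, Stata and R, can do this. It needs no new data and no change to the model. Standard errors rise by about 1% (1/0.99 = 1.01) to 6% (1/0.94 = 1.06), and the t multiplier widens intervals a little further.
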